### Interventions: modifications

Modifying the allocated intervention would require a revision surgery where the cochlear implant would be removed. Revision surgery is potentially harmful for the patient; therefore, it will only be performed in rare cases such as device failure, wound infection, or persisting pain.

### Interventions: adherence

The measurement scans will be performed on the same days as the regular follow-up visits of the medical rehabilitation program.

### Interventions: concomitant care

Not applicable, this study does not alter the regular care pathway.

### Outcomes

At intake, demographic data will be extracted from the electronic patient database: age, gender, if the deafness is pre- or postlingual, and electronic address. The following outcomes will be assessed at the baseline visit and follow-up visits at 1, 4, and 8 weeks and at 3 and 12 months postoperatively (Fig. 2). All measurements will be performed by the research team following the same protocol procedures.

**Fig. 2 Fig2:**
[figure not shown]
Schedule of enrolment, interventions, and assessments adapted from the Standard Protocol Items: Recommendations for Interventional Trials (SPIRIT). −t1: 2 weeks before surgery. t1: within 48 h of cochlear implantation. t2: 1 week post-surgery. t3: 4 weeks post-surgery. t4: 8 weeks post-surgery. t5: 3 months post-surgery. t6: 12 months post-surgery

#### Primary outcome measure

The main outcome of this study is R/S device migration and will be calculated by analyzing 3D reconstructions of the R/S device, acquired by cone-beam CT (CBCT) scans at baseline and during follow-up and at 12 months. We consider migration either translational or rotational above 1.0 mm or 1° as clinically relevant. Any migration under these cut-offs is considered within the measurement error margin of the analysis (0.3 mm or degrees). These calculations will be carried out by using 3DMedX® (v1.2.24.1, 3D Lab Radboudumc, Nijmegen). R/S positions will be superimposed, compared, and analyzed based on the Iterative Closest Point (ICP) algorithm [36]. The 3D reconstructions of the R/S device at baseline and 12 months will be compared to calculate the primary outcome measure.

#### Secondary outcome measures

##### Electrode migration

Electrode array migration is defined as a displacement of the basal electrode outside the cochlea of ≥ 1 mm (i.e., approx. 1 contact spacing). To compare the electrode array migration rate between the two surgical techniques, we will analyze the acquired CBCT scan images following a previously validated method [29, 37]. Electrodes, situated at the level of the round window, will be categorized as extracochlear, since electrodes at this position do not provide adequate stimulation or accurate pitch perception so that they mostly have to be removed from the stimulation map.

##### Electrode impedance values

Electrode impedance values will be measured by the patient’s audiologist at 1, 3, and 12 months after operation for all electrodes. This is according to regular care. Electrode impedance values measured in kOhm (a measure of the resistance to current flow) in common ground stimulation. Values above 20–30 kOhms will be considered abnormally high. Additionally, an increase of impedance values ≥75% from the averaged baseline after 1 month of activation will be considered a significant increase [29, 38].

##### Speech perception

Three months and 1 year after cochlear implantation, a conventional speech perception test with/without noise test will be performed with CVC words from the “Nederlandse Vereniging voor Audiologie” (NVA) word-list. Each list contains 11 words with a total of 33 phonemes. This is according to regular care. The speech tests can be quantified with a simple correct percentage score in bimodal solution if the patient has a hearing aid in the contralateral ear.

##### Complications

Incidence and degree of complications according to the following categories:

Device failure, which is classified into hard or soft failure using standardized criteria described in the 2005 Cochlear Implant Soft Failures Consensus Development Conference Statement [39].Major and minor complications according to the proposal of Hansen et al. [40].◦Major: a significant medical problem (e.g., meningitis), additional major surgery (e.g., cholesteatoma surgery or reimplantation due to a patient-related problem), explantation of the device for any reason other than device-related failure, any degree of permanent disability (e.g., facial nerve paralysis)◦Minor: complications leading to extended hospitalization or treatment on an outpatient basis, complications settling spontaneously or by conservative medical treatment, and complications managed by a minor surgical procedure (e.g., simple hematoma aspiration by syringe).

##### Questionnaire

The questionnaire used in this study is the validated COchlear iMPlant AwareneSS (COMPASS) survey that assesses patient-experienced burden by wearing the CI in their day-to-day activities [41]. It contains 15 items, multiple choice as well as visual analog scale items. Each item had a maximum score of 5, with a total maximum score of 75. A higher COMPASS score represents a higher awareness level. This questionnaire was developed in Utrecht and validated for use in the Dutch language. The questionnaire will be sent at 3 and 12 months postoperatively, by email through the data capture system Castor EDC to the study participants. If a patient does not wish to fill out the questionnaire online, it will be sent by post.

##### Validation of measurement method

The measurement technique to determine the position of the R/S device using a flexible tape measure, previously validated [35], will be compared to the results of migration measured by the CBCT scans. Repeated measurements will be done, and results will be compared to the results of migration measured by the CBCT scans.

### Participant timeline

All patients will undergo a high-resolution CBCT within 48 h after surgery, to assess the R/S device and electrode array position. Patients will undergo two more CBCT scans at 3 and 12 months postoperatively. The R/S device position will also be assessed with a validated external measurement method after 1, 4, and 8 weeks, and at 3 and 12 months postoperatively by a researcher or by the patients’ audiologist or speech therapist [35]. Patients will fill in a questionnaire after 3 and 12 months postoperatively. See Fig. 1 for an overview.

### Sample size

This sample size calculation was based on the primary outcome, R/S migration after 12 months. Due to limited quality evidence on the migration rate for both techniques, an estimation of the migration rates cannot be based on literature; therefore, we base our assumptions on clinical expertise [34, 42, 43]. We consider a migration under 1.0 mm or 1° to be clinically irrelevant. Migration under these cut-off points is within the measurement error margin of the measurement technique of the CBCT scan analysis. A sample size of 51 per study arm reaches 80% power (*β* = 0.8) and a significance level (*α*) of 0.05 with a non-inferiority margin of 1.0 mm. Standard deviation is estimated at 2.0 mm based on the database of Maxwell et al. [43]. In order to cover for possible loss to follow-up estimated at a maximum of 10%, we will include 56 patients per study arm.

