#### Trial design

This is a single-blind, non-inferiority randomized controlled trial, with two study arms (Fig. 1). Patients will be randomly allocated into equally sized groups: group A and group B (allocation ratio 1:1). Patients in group A will be operated with the bony recess technique, and patients in group B will be operated with the subperiosteal tight pocket technique. Inclusion in the study will have no consequence for the model or brand chosen by the patient, as is currently standard practice.

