### Randomization and blinding

Patients will be randomly assigned to one of the two study groups with 56 patients allocated in each group. Randomization takes place in the UMC Utrecht-endorsed electronic data capture system Castor EDC. (https://www.castoredc.com/). After giving informed consent, patients will be randomized with an allocation ratio of 1:1 and variable block sizes, with stratification for age (18–50 years, >50 years). Stratification is applied in both study groups. This is a single-blind study, meaning that only participants are blinded for the treatment allocation. The randomization will be done before surgery and patients will not be informed about the allocation. The research team is not blinded. The outcome data will be blindly analyzed. Blinding of the data will be performed by the electronic Case Report Form system used (see section “Data collection plan”). In the event that a revision surgery is necessary for removal or repositioning of the CI, unblinding is permitted. A member of the research team will inform the subject of the allocation.

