### Statistical analysis

To assess whether continuous variables are normally distributed, histograms and Q-Q plots will be computed. Continues data will be expressed as mean ± standard deviation (SD) when normally distributed, and as median ± interquartile range (IQR) when skewed. Number of cases and percentages will be presented as categorical variables. A *p*-value <0.05 is considered statistically significant. All analyses will be conducted according to the intention-to-treat principle.

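### The 51 per arm fits only a one-sided 5% non-inferiority test, which the sample size section does not declare and the analysis sections do not describe

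*Protocol article*

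**What the plan says.** The Trial design section of the protocol article states: "This is a single-blind, non-inferiority randomized controlled trial, with two study arms". Allocation is 1:1 (Randomization and blinding).

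The Sample size section bases the calculation on receiver/stimulator migration after 12 months: "A sample size of 51 per study arm reaches 80% power", at a significance level "of 0.05 with a non-inferiority margin of 1.0 mm". It adds: "Standard deviation is estimated at 2.0 mm". It does not say whether alpha is one- or two-sided, and it gives no expected difference between the arms. On the expected migration rates it says only that "we base our assumptions on clinical expertise".

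The Statistical analysis section sets one general rule for all analyses, a p-"value <0.05 is considered statistically significant", again without sidedness. The section on the primary objective names an unpaired t-test or a Mann-Whitney U test of the difference between groups. It mentions neither the 1.0 mm margin, nor a one-sided test, nor a confidence limit.

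**The concern.** In a non-inferiority trial the significance level fixes which confidence limit is compared with the margin. One-sided 5% corresponds to the upper limit of a 90% interval, and one-sided 2.5% to that of a 95% interval. The same data can pass on the first and fail on the second.

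The sample size section must have used one of these levels but does not say which. The analysis sections specify a conventional test of difference, for which the usual reading of p<0.05 is two-sided. The same rule also covers the secondary comparisons (COMPASS score, impedance, speech scores), where nothing suggests one-sided testing.

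Two things are at stake. The 80% power figure describes a decision rule that the analysis text does not contain. And the level of evidence for the main conclusion could still be chosen after the data are seen.

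**Working it through.** **Inputs.** Margin 1.0 mm, SD 2.0 mm, alpha 0.05, power 80%, 51 per arm and 56 per arm enrolled (Sample size); 1:1 allocation (Randomization and blinding). Assumption: true difference 0 mm, because the protocol states none.

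**Step 1: reproduce the stated figure.** Normal formula: n per arm = 2 × (z for alpha + z for power)² × SD² / margin².

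- One-sided 5%: 2 × (1.645 + 0.842)² × 4 / 1 = 49.5, so 50 per arm.
- One-sided 2.5% (two-sided 5%): 2 × (1.960 + 0.842)² × 4 / 1 = 62.8, so 63 per arm.

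**Step 2: exact t-test power.** Non-central t with df = 2n − 2 and non-centrality = margin / (SD × √(2/n)). At n = 51 this gives df = 100 and 1 / (2 × √(2/51)) = 2.525.

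| n per arm | One-sided 5% (90% CI) | One-sided 2.5% (95% CI) |
|---|---|---|
| 50 | 79.9% | 69.7% |
| 51 | 80.6% | 70.6% |
| 56 | 83.8% | 74.6% |
| 63 | 87.4% | 79.5% |
| 64 | 87.9% | 80.1% |

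At one-sided 5%, 51 is the first whole number to reach 80%, which matches the protocol exactly. At one-sided 2.5% the first is 64. The normal approximation at 51 gives 81.1% and 71.4%, so the choice of formula does not alter the picture.

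**Step 3: could 51 come from a two-sided level?** Only with an assumed advantage for the pocket. Solving 62.8 / (1 − d)² = 51 gives (1 − d)² = 1.231, so 1 − d = 1.11 and d = −0.11 mm. The protocol states no such advantage, so one-sided 5% with d = 0 is the simpler explanation.

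**Step 4: range for the assumed true difference.** Normal approximation at 51 per arm: SE = 2 × √(2/51) = 0.396 mm, and power = Φ((1 − d)/0.396 − z).

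- Pocket worse by 0.2 mm: Φ(2.020 − 1.645) = 65% and Φ(2.020 − 1.960) = 52%.
- Pocket better by 0.2 mm: Φ(3.030 − 1.645) = 92% and Φ(3.030 − 1.960) = 86%.

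Across this range the choice of level costs about 6 to 12 points of power; at d = 0 it costs about 10.

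**Step 5: set against the described analysis.** The named test asks whether the arms differ. If they are truly equal, a two-sided 5% test of difference is significant about 5% of the time, and a non-significant result does not establish non-inferiority. Neither 80% nor 71% is the power of that test. Both belong to a comparison with the 1.0 mm margin, which the analysis sections do not describe.

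**The case against.** The strongest reply is that nothing is miscalculated. Non-inferiority against a margin is a one-directional question, so alpha 0.05 stated next to a margin reads naturally as one-sided, and the exact match at 51 shows that this was meant. The sample size and analysis sections both give 0.05 and neither states sides, so they do not contradict each other on the number. A condensed article may also leave sidedness and interval level to the full protocol or analysis plan.

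Much of this stands. The 51 is correct for the test it presupposes, and missing sidedness alone would be a small clarity note. What remains is that the article does fix the primary analysis, as a test of difference at p<0.05 with no margin. Followed as written, it would not deliver the decision for which the trial was sized.

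A reader might go further in three ways that the document does not support:

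- **That the trial has only 71% power.** This is conditional. The protocol never says two-sided and contains no 95% interval.
- **That the sample size is an arithmetic error.** It reproduces exactly at one-sided 5%.
- **That 56 per arm fails to cover the stated loss**, since 56 × 0.9 = 50.4. In whole patients a loss within the stated 10% maximum is at most 5 of 56 (8.9%; a sixth would make 10.7%), which leaves 51. The section on secondary objectives also says that withdrawn participants are replaced.

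**Conclusion.** The point holds as a mismatch between the powered test and the described test. The 80% at 51 per arm is right for a one-sided 5% non-inferiority comparison with 1.0 mm (80.6%). That level is not declared, and the analysis sections describe neither it nor any comparison with the margin.

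If the decision were taken on a 95% interval instead, power would be 70.6% at 51 evaluable per arm and 74.6% at 56. With truly equal techniques, the chance of failing to show non-inferiority at 51 per arm would then be about 29% rather than the planned 20%.

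These figures assume a true difference of 0, an SD of 2.0 mm and a t-based comparison of means.

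**What to change.** In Sample size, state that alpha is one-sided 0.05 and that the true difference is assumed to be 0; 51 evaluable per arm then gives 80.6%.

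In Statistical analysis and its primary-objective section, state that the primary conclusion rests on the upper limit of the two-sided 90% confidence interval for the difference in mean migration at 12 months (pocket minus recess), with non-inferiority concluded if that limit lies below 1.0 mm. State separately which level and sidedness apply to the secondary comparisons.

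If a 95% interval is chosen instead, keep the enrolment and restate power as about 71% at 51 evaluable per arm (about 75% if all 56 are evaluable).

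Either route needs wording only and no extra patients, and should be settled before the outcome data are analysed. The first openly accepts a 5% rather than 2.5% risk of declaring non-inferiority when the true difference equals the margin. The second accepts a lower stated power.

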### Recruitment

Patient recruitment started in October 2021; we anticipate recruiting approximately 60 patients per year; thus, recruitment should be completed in 2 years. Patients are recruited from the outpatient Otorhinolaryngology department at the University Medical Center Utrecht. Eligible patients will be informed about the study by their treating physician. These patients have already been approved for cochlear implant surgery by the CI team. The investigator provides the patient with an information letter and informed consent form, which is signed by both the investigator and the patient before the surgery. Patients consent to the use of their data for the research purposes outlined in this protocol which includes publication of the results once the trial has been completed. Patients will not receive compensation for participation in the trial.

### Randomization and blinding

Patients will be randomly assigned to one of the two study groups with 56 patients allocated in each group. Randomization takes place in the UMC Utrecht-endorsed electronic data capture system Castor EDC. (https://www.castoredc.com/). After giving informed consent, patients will be randomized with an allocation ratio of 1:1 and variable block sizes, with stratification for age (18–50 years, >50 years). Stratification is applied in both study groups. This is a single-blind study, meaning that only participants are blinded for the treatment allocation. The randomization will be done before surgery and patients will not be informed about the allocation. The research team is not blinded. The outcome data will be blindly analyzed. Blinding of the data will be performed by the electronic Case Report Form system used (see section “Data collection plan”). In the event that a revision surgery is necessary for removal or repositioning of the CI, unblinding is permitted. A member of the research team will inform the subject of the allocation.

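### Blinded analysis is promised, but no safeguard described in the protocol covers the CBCT reading that produces the primary migration value

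*Protocol article*

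**What the plan says.** The *Randomization and blinding* section of the protocol article defines the blinding narrowly: "This is a single-blind study, meaning that only participants are blinded for the treatment allocation". It continues: "The research team is not blinded. The outcome data will be blindly analyzed". One mechanism follows: "Blinding of the data will be performed by the electronic Case Report Form system used", with a pointer to the *Data collection plan*. That section describes data extraction by research team members, password protection and user roles. It calls the assessors specialised and trained. It does not say that they are masked to allocation.

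On who measures, *Outcomes* says: "All measurements will be performed by the research team following the same protocol procedures". Two later sections qualify this. *Participant timeline* has the external (tape) measurement taken "by a researcher or by the patients’ audiologist or speech therapist", and *Electrode impedance values* assigns impedance to the patient's audiologist. None of these people is described as blinded.

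On where the primary value arises, *Primary outcome measure* says: "These calculations will be carried out by using 3DMedX". Positions are superimposed with the Iterative Closest Point (ICP) algorithm, and the 12-month reconstruction is compared with baseline.

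**The concern.** An eCRF can hide the arm from whoever runs the final test. The primary value, however, is generated from the scans in different software, by a team that the protocol calls unblinded. If the reader knows the arm, the reading can be influenced before any coded dataset reaches the analyst.

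The surgeon cannot be blinded in this trial. An image reader can be, at least in part, so the protection is available. Direction matters too: in a non-inferiority comparison, a reading shift that favours the tight pocket pushes towards declaring success. In addition, group A has a recess drilled in the skull that the CBCT images, so removing the arm label may not hide the arm completely. That the recess can be seen on the scan is an inference; the article does not say so.

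**Working it through.** **Text, set side by side**

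1. The team is unblinded and only participants are blinded (*Randomization and blinding*).
2. The team performs the measurements (*Outcomes*), apart from the named roles for the audiologist and speech therapist.
3. CBCT migration is calculated in 3DMedX (*Primary outcome measure*), not in the eCRF.
4. The eCRF is the only blinding mechanism named, and the section it points to describes no masking of assessors.

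Two readings are possible. If blinded analysis means only the final comparison, the CBCT reading is not covered. If it includes the reading (the article also uses the verb analyse for the 3D reconstructions), it conflicts with items 1 and 2, and no procedure supports it. The text needs repair on either reading.

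**Arithmetic: how sensitive the conclusion would be**

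Inputs from *Sample size*: margin 1.0 mm, SD 2.0 mm, 51 per arm, 80% power, significance level 0.05 (sidedness not stated).

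Reproducing the plan's figure, with a true difference of 0 and one-sided 0.05:
n = 2 × 2.0² × (1.645 + 0.842)² / 1.0² ≈ 49.5, so 50 per arm.
The noncentral-t calculation gives 51, with power 80.6%. At one-sided 0.025 the answers are 63 (normal) and 64 (t), so the stated 51 corresponds to one-sided 0.05.

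Standard error of the difference: 2.0 × √(2/51) = 0.396 mm.

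At a true excess of 1.0 mm in the pocket arm, a systematic reading shift b in the pocket's favour gives
P(false non-inferiority) = Φ(−1.645 + b/0.396).

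The shift sizes are assumptions. The last column repeats the calculation with 1.960 in place of 1.645.

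| b (mm) | b/0.396 | Argument of Φ | One-sided 0.05 | One-sided 0.025 |
|---|---|---|---|---|
| 0 | 0 | −1.645 | 5.0% | 2.5% |
| 0.1 | 0.252 | −1.392 | 8.2% | 4.4% |
| 0.2 | 0.505 | −1.140 | 12.7% | 7.3% |
| 0.3 | 0.757 | −0.887 | 18.7% | 11.5% |
| 0.5 | 1.262 | −0.382 | 35.1% | 24.3% |

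The 0.3 mm row has the same size as the measurement error margin given under *Primary outcome measure*. The article does not describe that margin as a bias, or as differing between arms.

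**The case against.** - **Single-blinding is declared openly.** For a surgical trial, an unblinded team with a coded dataset for the analyst is a coherent design. This stands, but it leaves the reading step uncovered, and it does not settle what the promise of blinded analysis includes.
- **Timing.** A reader might infer that blinding is applied only after the readings exist. The article never says when it is applied, so it does not prove that the reading step is unmasked. What it shows is that no safeguard for that step is described.
- **Who measures.** A reader might infer that the unblinded research team makes every measurement. *Electrode impedance values* and *Participant timeline* show otherwise, although the staff they name are not described as masked either.
- **Room for judgement.** A reader might infer that segmentation and the choice of registration region depend on operator judgement. The article does not say so. It describes ICP superimposition, which leaves less discretion than manual reading. How much remains is unknown.
- **Magnitude.** The table assumes a shift in one direction and in one arm. It also assumes a non-inferiority test on the mean, whereas *Statistical analysis primary objective* gives an unpaired t-test or Mann-Whitney test and states no confidence bound. These limits stand; the figures show sensitivity and do not predict a bias.
- **Condensed article.** Imaging detail is commonly left to the full protocol. That would answer a point about silence, but here the article states who is unblinded, who measures and how blinding is done.
- **Tape reading.** It is manual and so more exposed, but it serves a secondary validation aim and does not carry the primary conclusion.

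**Conclusion.** The point holds in a limited form. As written, no described safeguard covers the CBCT reading that produces the primary value, and extending the promise of blinded analysis to that reading would conflict with the statements that the team is unblinded and performs the measurements.

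The article does not support saying that biased reading has occurred or is likely, or that false non-inferiority will be 19%. Under the assumptions above, it would be about 8% to 35% for assumed shifts of 0.1 to 0.5 mm, against a nominal 5%. Those figures rest on SD 2.0 mm, 51 per arm, one-sided 0.05, a true excess equal to the margin, and a shift wholly in the pocket's favour. ICP registration may keep any real shift smaller. The change should be made because it is cheap and the primary outcome depends on this step; it does not affect the sample size.

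**What to change.** 1. Export each scan pair under a random code, in random order and without an arm label.
2. Run the 3DMedX superimposition with one prespecified skull registration region away from the implant bed, the same in both arms.
3. Lock the millimetre and degree values before allocation is linked.
4. Where feasible, have the tape readings taken by the audiologist or speech therapist already named in *Participant timeline*, without telling them the arm.
5. State who reads the scans and whether they are masked, and reconcile *Outcomes* with the sections that name other measurers. Limit the claim of blinded analysis to what is actually masked, and acknowledge that a drilled recess may still be visible on the scan.

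No additional reader or visit is needed. The cost is some added handling time per scan. Masking may remain partial for the reason given in item 5.
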